# 9. ETHICAL CONSIDERATIONS

## 9.1 Regulation statement

It is the responsibility of the investigator to obtain Medical Ethics Committee approval in writing, prior to the study start. A new approval for Medical Ethics Committee is required for any amendment or revision of the Clinical Investigation Plan affecting the intent and principles of the study or other ethical aspects. The investigator will maintain all correspondence with the Medical Ethics Committee.

## 9.2 Recruitment and consent

All patients have to review, understand, agree to, and personally sign and date the Informed Consent form prior to enrolment in the study. In case of subjects’ incompetence, a guardian or legal representative will have to assume the subjects role for the Informed Consent Procedure.

Informed Consent forms will be signed and dated by a medical doctor, or a Clinical Research Associate (CRA), authorised by the main investigator. The patient receives a copy of the Informed Consent form and the original form is filed in the study file.

## 9.3 Compensation for injury

The LUMC has a liability insurance which is in accordance with the legal requirements in The Netherlands (Article 7 WMO and the measure regarding Compulsory Insurance for Clinical Research in Humans of 23th June 2003). This insurance provides cover for damage to research subjects through injury or death caused by the study.

1. € 450.000 for death or injury for each subject who participates in the research;

2. € 3.500.000 for death or injury for all subjects who participates in the research;

3. € 5.000.000 for the total damage incurred by the organisation for all damage disclosed

by scientific research for the sponsor as ‘verrichter’ in the meaning of said Act in each year of insurance coverage.

The insurance applied to the damage that becomes apparent during the study or within for years after the end of the study.

De verzekeraar van het onderzoek is:

Name:  CentraMed

Adress:  [name]

Tel.nr.: [name]

## 9.4 Incentives

Not applicable

# 10. ADMINISTRATIVE ASPECTS AND PUBLICATION

## 10.1 Handling and storage of data and documents

All personal data will be stored like the rest of the medical data according to the rules in our hospital. Only the investigation group has access to the source data of this study. Data will be kept until 15 years after finishing the study. When data will be used for publication they will never relate to individual traceable patients.

## 10.2 Amendments

Amendments are changes made to the research after an approval by the accredited METC has been given. All amendments will be notified to the METC that gave the approval.

A ‘substantial amendment’ is defined as an amendment to the terms of the METC application, or to the protocol or any other supporting documentation, that is likely to affect to a significant degree:

- the safety or physical or mental integrity of the subjects of the trial;
- the scientific value of the trial;
- the conduct or management of the trial; or
- the quality or safety of any intervention used in the trial.

All substantial amendments will be notified to the METC that gave a favourable opinion.

## 10.3 Annual progress report

The sponsor/investigator will submit a summary of the progress of the trial to the accredited METC once a year. Information will be provided on the date of inclusion of the first subject, numbers of subjects included and numbers of subjects that have completed the trial, serious adverse events/ serious adverse reactions, other problems and amendments.

## 10.4 End of study report

The investigator will notify the accredited METC at the end of the study. The end of the study is defined as the last patient’s last visit.

In case the study is ended prematurely, the investigator will also notify the accredited METC, including the reasons for the premature termination.

Within one year after the end of the study, the investigator will submit a final study report with the results of the study, including any publications/abstracts of the study, to the accredited METC.

# APPENDIX 1: PROTOCOL RESTRICTIVE TRANSFUSION POLICY

Patients younger than 60 years

Within 4 hours after surgery More than 4 hours after surgery

Hb  4,0 mmol / l = 0 packed cell Hb  4,0 mmol / l = 0 packed cell

3,0 - < 4,0 = 1 packed cell 3,5 - < 4,0 = 1 packed cell

< 3,0 = 2 packed cells < 3,5 = 2 packed cells

Patients older than 60 years

Within 4 hours after surgery More than 4 hours after surgery

Hb  4,5 mmol / l = 0 packed cell Hb  5,0 mmol / l = 0 packed cell

4,0 - < 4,5 = 1 packed cell 4,5 - < 5,0 = 1 packed cell

< 4,0 = 2 packed cells < 4,5 = 2 packed cells

Patients with increased risk (because of co-morbidity)

Within 4 hours after surgery More than 4 hours after surgery

Hb  5,5 mmol / l = 0 packed cell Hb  6,0 mmol / l = 0 packed cell

5,0 - < 5,5 = 1 packed cell 5,5 - < 6,0 = 1 packed cell

4,5 - < 5,0 = 2 packed cells 5,0 - < 5,5 = 2 packed cells

< 4,5 = 3 packed cells < 5,0 = 3 packed cells

**In all cases these are transfusion guidelines, of which the clinical presentation of the patient is of greater importance to which transfusion policy is followed.**

# APPENDIX 2: DEFINITIONS POSTOPERATIVE INFECTIONS

1: Symptomatic urinary tract infections (UWI):

a) Positive urine culture with at least 1 clinical symptom of UWI *, or

b) At least 2 symptoms of UWI * with or

1) Urine positive in Gram-staining, or

2) Urine positive for leucocytes, or

3) Urine dipstick for nitrate or WBC esterase positive, or

4) Diagnosis UWI by clinician, or

5) Specific UWI therapy started by clinician

2: Asymptomatic UWI:

a) Positive urine culture with stay catheter or

b) Two positive urine cultures

3. Wound infections:

a) Purulent wound fluid, or

b) Positive wound culture, or

c) Diagnosis wound infection by clinician **, or

d) At least one symptom of wound infection # with or

1) Conscious open wound made by the clinician, or

2) Spontaneous dehiscence of the wound

4: Pneumonia:

a) Crepitating or damping by percussion and

1) Positive blood-, bronchi- or bronchus biopsy culture with known respiratory pathogens, or

2) New purulent sputum or change in sputum appearance

b) X- thorax conforming pneumonia and

1) Positive cultures as above, or

2) Changes in sputum as above

5: Bacteraemia:

Positive blood culture with fever

* Symptoms of UWI: frequent free urge; dysurie; suprapubic pain; fever

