This study proposal may provide evidence based support for improved postoperative rehabilitation by using CS after total knee surgery and will contribute to optimal blood product management in orthopaedic surgery patients. The mechanism for this improved rehabilitation may by through reduction of the intra-articular bleeding, resulting in subsequent reducing postoperative pain and facilitating earlier postoperative functional improvement i.e. faster gain of knee flexion and knee extension. Sanquin’s centre for clinical research located at the Blood Bank Region Southwest approves designs and coordinates randomised controlled trials (RCT) together with principle investigators. Initiated from this collaboration, this project is a continuation of previously completed clinical research projects (TOMaat, Trigger & Drain studies) with the department of orthopaedic surgery of the LUMC (head: prof.dr. [name]) and Sanquin researchers. The main objective of these studies was to define optimal transfusion management in orthopaedic surgery: Transfusie op Maat: ‘TOMaat study’. The infrastructure of the TOMaat trial can be used for the current question; on the clinical effectiveness, postoperative pain and early knee function of CS use in knee surgery.

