# Symptoms of wound infection: pain; sensitive, local swelling, local warm and fever

** Referentie: W.J.Gaine et al., JBJS 2000; 82(4): 561-565

Addendum of FIRST protocol vs 4.1

dd 15 May 2013.

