1. Is there a difference in postoperative complications (LoS, bleeding, pain, body temp.( if applicable)) with **reinfused autologous wound drain salvage** and no reinfused drain fluid after wound catheter use,
2. Costs calculation (hospital stay) of **drain use (all, incl. no autologous reinfusion) vs no drainage**, low-vac vs Bellovac vs no drainage (only Bronovo uses Bellovac, n=73),
3. postoperative QoL outcomes and drain use (all, incl. no autologous reinfusion)

List of postoperative outcomes (after 6 wk and 1 jaar)
- VG
- Medication
- Hand power
- BMI
- Barthel
- Oxford Knee Score
- KOOS
- SF12
- IPQ-K
- EQ5D
- Knee Society Score

Postoperative outcomes at hospital stay
-Postop complications, such as infections (deep and superficial wound infection, lung and urinary track infections),

-ROM and pain scores

-Postoperative bleeding

-Total hospital stay
-After two weeks: ROM, complicaties, pijnscore, Barthel, EQ5D, Oxford Knee

-Transfusion use: RBC transfusions, indications, triggers or type transfusion products
-Surgery time

Leiden, 15 May 2013

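### Wound-infection criterion 3d counts culture-negative haematoma openings and aseptic dehiscences as infections, so a CryoSeal effect on bleeding could shift the descriptive infection comparison

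*Combined protocol and SAP*

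**What the plan says.** Appendix 2, item 3, gives four routes to a wound infection, joined as alternatives:

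- 3a: "Purulent wound fluid, or"
- 3b: "Positive wound culture, or"
- 3c: a clinician's diagnosis, with a footnote to a cited article
- 3d: "At least one symptom of wound infection # with or" one of two events. The first is "Conscious open wound made by the clinician, or" and the second is spontaneous dehiscence.

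The footnote to 3d reads "Symptoms of wound infection: pain; sensitive, local swelling, local warm and fever". Any one item on that list is enough.

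Section 6 (Study parameters and endpoints) makes complications a secondary endpoint. Section 8 compares adverse events between arms by Fisher's exact test. The addendum's list of outcomes at hospital stay includes "Postop complications, such as infections (deep and superficial wound infection, lung and urinary track infections", with postoperative bleeding as a separate entry. Section 1 gives the expected mechanism as "reduction of the intra-articular bleeding, resulting in subsequent reducing postoperative pain".

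**The concern.** Criterion 3d does not ask why the wound was opened and makes no exception for a negative culture. Taken as written, a wound opened to evacuate a haematoma, cultured negative and painful, is a wound infection. So is an aseptic dehiscence with local swelling. Both are better described as bleeding or wound-healing complications.

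This matters more here than in most trials because bleeding at the wound is what CryoSeal is meant to change. If it reduces the number of haematomas that are opened, the 3d count falls in that arm with no change in infection. Pain is also a qualifying symptom, and less pain is part of the proposed mechanism. Blinding does not remove the problem, since a genuine bleeding effect would move the count under perfect blinding. If instead openings are equal in the two arms, the non-infections dilute any real infection difference.

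**Working it through.** **Logic (no assumed rates).** Write a, b and c for 3a to 3c, s for at least one listed symptom, o for opened and h for dehisced. The rule is: infection = a or b or c or (s and (o or h)). I read the wording of 3d as symptom with either event, as in item 1b of the same appendix. Of the 64 combinations, those positive under the full rule but negative under a or b or c are:

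| a | b | c | s | o | h |
|---|---|---|---|---|---|
| 0 | 0 | 0 | 1 | 1 | 0 |
| 0 | 0 | 0 | 1 | 0 | 1 |
| 0 | 0 | 0 | 1 | 1 | 1 |

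Every wound that 3d adds therefore has no pus, no positive culture and no clinician diagnosis. Here b = 0 covers two situations: cultured with a negative result, and never cultured.

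**Contrast within the appendix.** The symptom-based urinary route, 1b, needs two symptoms plus a Gram stain, leucocytes, a dipstick result, a clinician's diagnosis or started therapy. Route 3d needs one symptom and no evidence of that kind.

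**Illustration.** The documents give no rates of wound infection, haematoma opening or dehiscence, so all rates here are assumptions. Only n = 250 per arm comes from the protocol (section 4.4). The illustration also assumes that 3a to 3c catch every true infection and that every 3d-only wound is sterile, which makes it an upper-end case.

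Counted rate = true infection rate + sterile opening or dehiscence rate × P(at least one symptom).

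True infection 2% in both arms; sterile events 2% control, 1% CryoSeal; P = 0.9 to 1.0:

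- Control: 2% + 2% × 0.9 = 3.8%, up to 2% + 2% × 1.0 = 4.0%. Per 250 that is 9.5 to 10.0 counted, against 5.0 true.
- CryoSeal: 2% + 1% × 0.9 = 2.9%, up to 3.0%. Per 250 that is 7.25 to 7.5.
- Risk ratio: 2.9/3.8 = 0.76 to 3.0/4.0 = 0.75, with a true value of 1.00.

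Varying true infection over 1–3% and control sterile events over 1–3% (halved by CryoSeal), same P:

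- Inflation of the control rate: from (3% + 0.9%)/3% = 1.3 to (1% + 3%)/1% = 4.0.
- Risk ratio: from 3.45/3.9 = 0.88 down to 2.5/4.0 = 0.625.

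**Chance of a significant result.** Fisher's exact test, two-sided 5%, 250 per arm, summed over the binomial distributions:

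| Control | CryoSeal | P(reject) |
|---|---|---|
| 4.0% | 4.0% | 3% |
| 4.0% | 3.0% | 6% |
| 4.0% | 2.5% | 10% |

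Rejection becomes common only under more extreme inputs. With 1% true infection and 5% sterile events cut by 75%, the rates are 6.0% against 1% + 1.25% = 2.25%, and the test rejects in about 49% of trials.

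**The case against.** The strongest reply has five parts.

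1. *A reader might infer that 3d adds only sterile wounds.* The documents do not support that. A wound with no positive culture may never have been cultured, and 3d can catch a real infection that nobody swabbed or labelled. This stands. If a share f of 3d-only wounds are true infections, a 2% rate of such wounds gives 250 × 2% × (1 − f) false counts in control: 5.0 at f = 0 but 2.5 at f = 0.5.
2. *The symptom condition may filter more than supposed.* Section 6 has pain scored daily until discharge, which shows that it is measured, not that it is present when a wound is opened. The 90–100% figure is an assumption. Even so, pain or swelling alone meets the condition, and nothing tells the assessor to discount ordinary surgical pain.
3. *A reader might infer that the planned safety test is biased.* Section 8 tests adverse events, and an opened haematoma or a dehiscence is an adverse event whatever its label. That comparison need not change. The addendum's infection entry is in an outcome list that follows research questions described as post-hoc, and no between-arm test of wound infection is specified. Sections 6 and 8 and the addendum do not cite Appendix 2, so its use for that entry is inferred from its title. All of this stands. Postoperative bleeding is also listed separately, so a bleeding effect would be visible beside the infection count.
4. *A reader might infer that a false infection claim is likely.* At the moderate assumed rates it is not: about 6–10%.
5. *The reach of 3c cannot be judged.* It refers to an outside source, so how many wounds are left to 3d alone is unknown.

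These points limit the consequence. They do not change the classification of a wound that was cultured, found negative, and never diagnosed as infected: the written rule calls it an infection.

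**Conclusion.** The concern holds in a limited form. As written, 3d adds a mixed group that includes culture-negative haematoma openings and aseptic dehiscences, and no section narrows the criterion or provides for adjudication. Because CryoSeal is aimed at bleeding, the descriptive wound-infection comparison could move without any change in infection. The logic rests on the text alone. The size does not: a spurious risk ratio of about 0.63 to 0.88 follows only from assumed rates and from treating every 3d-only wound as sterile. The likely harm is a misleading estimate and a mislabelled safety table rather than a false significant finding. The primary extension endpoint is unaffected. The change is worth making because it is cheap and loses no safety information.

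**What to change.** Before de-blinding, add to item 3d that a wound that was cultured with a negative result and meets none of 3a to 3c is not counted as a wound infection, but is coded as a bleeding or wound-healing complication. Keep uncultured 3d-only wounds in the infection count, since some may be real infections. In the addendum, tabulate all 3d-only events separately by arm and report the infection comparison with and without them.

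The rule uses the culture result and does not depend on the reason for opening, which section 6 does not list among the data collected. The cost is two or three sentences and blinded recoding of what should be a small number of wound events, provided that culture results can be retrieved. The downside is a slightly less sensitive infection count; the separate table keeps the recoded events visible. This changes outcome coding only, not clinical management.

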# Symptoms of wound infection: pain; sensitive, local swelling, local warm and fever

** Referentie: W.J.Gaine et al., JBJS 2000; 82(4): 561-565

Addendum of FIRST protocol vs 4.1

dd 15 May 2013.

**Analysis plan**

The study database will be closed and subsequently be de-blinded more than six weeks after the last surgery procedure of the FIRST-patients. This analysis plan will be registered at the Dutch trial register (NTR) and the ethics committee will be informed about protocol 4.1 before execution of the plan using the data from the closed database. The primary analysis will be performed as stated in the protocol. Subsequently, a for three variables stratified subgroup analyses of the primary end points will be performed. This will be folllowed by a pre-specified subgroup analyses using 19 variables for hypothesis screening.

Statistical analyses

In SPSS, for each subgroup the odds ratio (OR under randomized controlled conditions) or relative risk (by univariate- and multivariate analysis (MVA)) with the corresponding 95% confidence interval (CI) will be estimated for CryoSeal. Although subgroups of the study population are predominately formed based on confounding factors, we will investigate the stability of the effect estimates over different levels of the confounding factors by correction in the MVA for those confounders. When a preoperative variable is significantly associated with CrySeal use we will address this observation, however we continue the primary and secondary analysis using the pre-specified subgroups.

Confounding and effect modification

Normally the problem of confounding by indication is virtually absent in the study of side effects of medical interventions. In case of CryoSeal use however, the subgroup analyses does not correct for the possibility of effect modification. Effect modification could arise since patients when for example wound drains were placed and could change the susceptibility of the patients for effects by CryoSeal.

Interpretation of pre-specified subgroup analyses and “multiple testing”

The stratified subgroup analyses will be made with each pre-specified subgroups. There will be no correction for multiple testing because all subgroups are defined by variables which are known to have underlying associations with the primary endpoints of the study. All subgroups were specified before the data are available. The implications of the outcomes will be discussed in relation to all other associated estimates observe in all subgroups.

The Plan of pre-specified subgroup analyses

Subgroup analyses:

After subsequent primary and secondary analysis of the effect of CryoSeal using the primary and secondary endpoints as presented in Protocol 4.1 of the total RCT dataset, according to intention to treat (ITT) and according to treatment (ATT), also pre-specified subgroup analyses of the putative effects on the primary and secondary endpoints (estimated odds ratio (OR) and 95% interval between both study-arms) of CryoSeal will be performed.

1. The following hypotheses will be tested using three for the variables stratified subgroups:

1. Catheter use and no catheter use
2. NSAID-users and no NSAID-users
3. Age > 70 and ≤ 70 years, or categorized in 3 equal sized samples of age (for example: <60, 60-70, >70)

The corresponding hypotheses are:

1. Catheter can disturb the CS-sealing process of the wound and therefore decrease the postoperative knee ROM and mobility effect of CS

2. NSAID-use are prescribed to reduce pain perception and as anti-coagulation medication, which decrease postoperative knee ROM and mobility effect of CS

3. Age is associated with increased co-morbidity resulting in reduced wound healing, which increase postoperative knee ROM and mobility effect of CS in patients > 60 years

2. Separated in the CryoSeal arm and in the non-CryoSeal patients the following 19 pre-specified subgroups will be selected for MVA to identify whether these factors are important or not in the CS-effect. Subsequently, using the total study cohort de following subgroups are analysed by dichotomic (or continuous) comparison (Y/N) between CryoSeal use or not:

Combined subgroups using 4 variables:

1. Catheter use and no catheter use
2. NSAID-users and no NSAID-users
3. Age > 70 and ≤ 70 years, or categorized in 3 equal sized samples of age (for example: <60, 60-70, >70)
4. Women and men

Single subgroups using each variable (or not):

1. Peroperative Hb ≤ 6 mmol/L and > 6 mmol/L
2. Transfused and non transfused patients
3. Prednison-users and no Prednison users
4. Cemented and no cemented protheses
5. “Bloedleegte” surgery and no “bloedleegte” surgery
6. If catheter use: Bellovac and no low-vac catheter use
7. If transfused: trigger of perioperative RBC use at Hb ≤ 6 mmol/L and > 6 mmol/L
8. If transfused: Age> 60 and age ≤ 60 with trigger of perioperative RBC use at Hb ≤ 6 mmol/L
9. Surgery time > 2 hr and < 2 hr

Stepwize variables:

1. When drain used: Wound salvage production or not (Y/N)
2. When salvage production, reinfusion or not

Continuous variable:

1. Hospital stay in days
2. Years of age

Categorized variables

1. Hospital stay: <3; 3-5; 6-8; >8 days
2. Age: >70; 70-60; <60 years of age

The subgroup analyses above are explorative for hypotheses screening.

Extra secondary analyses: Observational analyses of the RCT dataset:

When no correlation between the use of CryoSeal and the pre-, peri- and postoperative variables can be demonstrated and the above estimates are homogenous over the study arms, they will be pooled over the strata before further subgroup analysis; univariate followed by subsequent multivariate analysis will be performed.

The following research questions will be investigated by post-hoc analyses:

Preoperative variables:

1. Is there a correlation between preoperative hand grip strength and postoperative complications after > 1 year?
2. Are there associations between pre-op outcomes of the questionnaires and post-op functional/QoL/complications?
3. Is there a correlation between Range of Motion (ROM) and Oxford Knee Score outcomes?
4. Is there a correlation between preoperative NSAID (incl. Asperin) use and primary and secondary outcomes?
5. Is there a correlation between preoperative Prednison use and primary and secondary outcomes?

Perioperative variables:

1. Is there difference in post-op outcomes between LPS cemented vs cementless (Haga vs Spaarne) knee protheses
2. Is there difference in post-op outcomes (incl. hospital stay, body temp. (if applicable)) or -complications (incl. transfusion reactions) in transfused and non-transfused patients, or patients transfused at different indications/-triggers, and using different type of transfusion products
3. Are there more transfusion reactions in women?
4. Is there a difference in primary and secondary outcome between surgery type (“onder bloedleegte” or not)
5. Is there a difference in mean hospital stay and EPO use (if applicable)
6. Is there a correlation between wound catheter (incl. autologous reinfusion, if applicable) use vs no use and postoperative complications (bleeding, body temp).
7. Is there a correlation between perioperative wound drain reinfusion vs no reinfusion (if applicable) and postoperative complications
8. Is there a correlation between surgery time and postoperative outcomes of the questionnaires
9. Blood losses associated with type of catheter used
10. Is there a correlation between perioperative transfusion trigger (anaemia), age and length of hospital stay

Postoperative variables:

1. Is there a difference in postoperative complications (LoS, bleeding, pain, body temp.( if applicable)) with **reinfused autologous wound drain salvage** and no reinfused drain fluid after wound catheter use,
2. Costs calculation (hospital stay) of **drain use (all, incl. no autologous reinfusion) vs no drainage**, low-vac vs Bellovac vs no drainage (only Bronovo uses Bellovac, n=73),
3. postoperative QoL outcomes and drain use (all, incl. no autologous reinfusion)

List of postoperative outcomes (after 6 wk and 1 jaar)
- VG
- Medication
- Hand power
- BMI
- Barthel
- Oxford Knee Score
- KOOS
- SF12
- IPQ-K
- EQ5D
- Knee Society Score

Postoperative outcomes at hospital stay
-Postop complications, such as infections (deep and superficial wound infection, lung and urinary track infections),

-ROM and pain scores

-Postoperative bleeding

-Total hospital stay
-After two weeks: ROM, complicaties, pijnscore, Barthel, EQ5D, Oxford Knee

-Transfusion use: RBC transfusions, indications, triggers or type transfusion products
-Surgery time

Leiden, 15 May 2013

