## 4.4 Sample size calculation

We performed a sample size calculation for our primary outcome which is pre- to postoperative difference in knee extension angle at two weeks after surgery. We expect to find a difference between study arms of 10 degrees, which we also feel is clinically relevant. We have little prior data to base our calculations on, but we expect a standard deviation of 35 degrees in our primary outcome. We conclude that we need 250 patients in each arm to be able to detect the stated difference at significance level 4.9% with 90% power.

We have made a slight adjustment to the usual significance level of 5% because we plan to perform an interim analysis when a total of 250 patients have been included. At this time we will decide if the trial should be terminated early for efficacy or futility. If the trial continues, we will use the available data to estimate the standard deviation of the primary outcome. Based on this estimate, we will re-compute the sample size that is needed to achieve 90% power to detect a 10 degree difference between the study arms at level 5%. We will adjust the sample size accordingly. However, we will not include less than 400 patients or more than 600 patients.

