# 6. METHODS

## Study parameters and endpoints

Hypothesis

The hypothesis is that the application of CryoSeal (CS) during total knee replacement surgery is beneficial for the patient with respect to a faster track and improved postoperative rehabilitation. The beneficial effect may be due to quicker rehabilitation, by pain reduction, better mobilisation and quality of life (especially short time).

Primary endpoints

- postoperative knee function in extension difference as compared with preoperative extension function with goniometric at 2 and 6 weeks (in relation to secondary endpoints)

Secondary endpoints

- Grade flexion and extension difference after surgery
- Drain use or not
- Postoperative Hb/Ht
- Number of transfusions after surgery (according to appendix 1)
- Pain score
- Complications
- Total hospital stay and duration of rehabilitation
- Illness perception IPQ-K score
- Function improvement score (KSS, Barthel Index score, KOOS etc. see flowchart)
- Hand grip strength (measured with (Jamar) hand dynamometer)
- Activity Monitor

Study parameters

- Demographic data; gender, birth date (age), weight, length (BMI)
- Medical History; underlying diseases and home medication (including use of antibiotics prophylaxis and NSAIDs)
- Laboratory analysis; haemoglobin, haematocrit and blood view, CRP and erythrocyte sedimentation rate
- Operation details; anaesthesia, start- and end time of surgery, surgeon, type and time point placing and opening of drain, use of heparin, information about application of CryoSeal (if applicable), knee function after implantation of the implants
- Clinical data; number of transfusions (red cells, platelets and plasma), complications, removing drain, amount collected in drain, medication (including use of antibiotics and NSAIDs), discharge date
- Pain (score) at 24h post operative, and at 8:00 h each day until discharge from hospital.
- Rehabilitation; knee function during the first postoperative days, Barthel Index score and standard knee function scores (see Table 1).

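### The addendum plans odds ratios or relative risks for endpoints measured on continuous scales, looks for effect modifiers within each arm, and specifies no interaction test for NSAID use or age

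*Combined protocol and SAP*

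**What the plan says.** Protocol section 6, Study parameters and endpoints, defines the primary endpoint as "postoperative knee function in extension difference as compared with preoperative extension function with goniometric at 2 and 6 weeks". Section 8 analyses it by ANCOVA on the angle, adjusted for the preoperative angle, two-sided at 0.049. Section 8 also adds drain use and a drain-by-CryoSeal interaction to that model. For other patient groups it names no interaction term.

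The addendum (Analysis plan, 15 May 2013) keeps the protocol's primary analysis and then adds subgroup work:

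- **Effect measure.** Under Statistical analyses it estimates "for each subgroup the odds ratio (OR under randomized controlled conditions) or relative risk (by univariate- and multivariate analysis (MVA" with 95% confidence intervals. Under Subgroup analyses it applies this to the primary and secondary endpoints: "estimated odds ratio (OR) and 95% interval between both study-arms".
- **Three hypotheses.** Catheter use, NSAID use and age are each said to change the effect of CryoSeal on knee motion and mobility. They are to be tested in stratified subgroups.
- **Nineteen variables.** "Separated in the CryoSeal arm and in the non-CryoSeal patients the following 19 pre-specified subgroups will be selected for MVA", to see whether they matter for the CryoSeal effect. A comparison of CryoSeal use or not in the total cohort follows.
- **Multiplicity.** The addendum waives adjustment: "no correction for multiple testing because all subgroups are defined by variables which are known to have underlying associations". The association it means is the one between each variable and the primary endpoints. After the 19-variable list, the subgroup analyses are labelled explorative.

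**The concern.** **Scale.** An odds ratio or relative risk needs a yes/no outcome. Neither document defines a responder or a cut-off for extension, or for pain, KOOS, Oxford Knee Score, SF-12 or EQ5D. Someone would have to choose cut-offs later. That loses information and puts the subgroup results on a different scale from the main result.

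**Within-arm models.** All three hypotheses are about effect modification: does the CryoSeal effect differ between levels of a factor? A regression fitted in one arm shows whether the factor predicts outcome in that arm. Comparing two such regressions by eye does not test whether the treatment effect differs. The total-cohort step that follows names no interaction term, and the addendum's own text on confounding concedes that the subgroup analyses do not correct for effect modification. Catheter, NSAID use and age also head the 19-variable list (4 + 9 + 2 + 2 + 2 = 19), so they pass through this step as well.

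**Multiplicity rationale.** A known association with the endpoint makes a variable prognostic. It gives no protection against false claims that the treatment effect differs by that variable.

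At stake is whether the subgroup conclusions on NSAID use and age, and the screening results, can be interpreted.

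**Working it through.** **Inputs from protocol section 4.4.** Difference: "We expect to find a difference between study arms of 10 degrees". Spread: "we expect a standard deviation of 35 degrees in our primary outcome". Size: "we need 250 patients in each arm to be able to detect the stated difference at significance level 4.9% with 90% power".

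**Assumptions, not in the documents.** Subgroup splits of 50/50 or 30/70, normally distributed outcomes, two-sided 0.05 for subgroup tests, and independent tests where stated.

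**1. The plan's own figure.** n per arm = 2 × (35/10)² × (1.969 + 1.282)² = 259, against the stated 250. Power at 250 per arm is Φ(10/(35√(2/250)) − 1.969) = Φ(3.194 − 1.969) = 89%. The gap is small and does not bear on this point.

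**2. Cost of a dichotomy in one stratum.** A 50/50 split leaves 125 per arm.
- In degrees: SE = 35√(2/125) = 4.43; power = Φ(10/4.43 − 1.96) = Φ(0.299) = 62%.
- Cut at the control median: responders are 50.0% against Φ(10/35) = 61.2%. SE of the difference = √((0.250 + 0.237)/125) = 0.0624; power = Φ(0.1125/0.0624 − 1.96) = Φ(−0.159) = 44%.

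**3. Ratio measures with a constant 10-degree effect.**
- Stratum with 50% control responders: 61.2% on CryoSeal, RR 1.22, OR 1.58.
- Stratum with 15.9% control responders (cut 1 SD above the control median): 23.8% on CryoSeal, RR 1.50, OR 1.65.

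The effect in degrees is the same in both. The RR differs clearly, the OR only a little.

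**4. Within-arm models when there is no interaction.** Take a factor split 50/50, 250 patients per arm, with the same prognostic effect in both arms. If p is the chance of significance in one arm, the chance that exactly one arm is significant is 2p(1 − p).

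| Prognostic effect | p | Exactly one arm significant |
|---|---|---|
| 0 degrees | 5.0% | 9.5% |
| 5 degrees | 20.4% | 32% |
| 10 degrees | 61.7% | 47% |

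These figures apply if significance is compared between arms. The addendum states no decision rule.

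**5. Which hypotheses have an interaction test?**
- Catheter: yes, through section 8, if catheter means the wound drain. The addendum's later questions, which speak of wound catheters and drains together, suggest that it does.
- NSAID use: none named.
- Age: none named. The grouping is left open between above/up to 70 and three equal-sized groups, while the hypothesis concerns patients over 60.

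**6. Multiplicity.** Three independent tests at 0.05: 1 − 0.95³ = 14.3%.

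**7. Power of a proper interaction test.** N = 500, true interaction 10 degrees, SE = 35√(4/(500f) + 4/(500(1 − f))), where f is the share in one subgroup.
- f = 0.5: SE 6.26, power Φ(1.597 − 1.96) = 36%.
- f = 0.3: SE 6.83, power Φ(1.464 − 1.96) = 31%.
- At 0.05/3 = 0.0167 (critical value 2.394): 21% and 18%.

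**The case against.** The strongest reply is that this is secondary work and partly covered elsewhere. The primary analysis stays an ANCOVA in degrees, and its error rate is untouched. Section 8 already has the right test for drain use. The three hypotheses get between-arm estimates within strata, the within-arm models belong to the 19-variable screen, and a total-cohort comparison follows. The addendum calls the subgroup work explorative, reports intervals, and says that findings will be discussed in relation to all the other subgroup estimates. Odds ratios and relative risks suit binary outcomes such as complications or transfusion.

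Much of this stands, and it rules out stronger readings that a reader might infer:

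- **That the subgroup results can answer none of the hypotheses.** The drain hypothesis has a suitable test.
- **That the main comparison loses power.** A median cut on all 500 patients would lower it from 89% to about 71–72%, but no such analysis is planned.
- **That false claims reach about 26% over three factors and two time points.** That figure treats the 2- and 6-week values of the same patients as independent, which is implausible.
- **That formal multiplicity control is obligatory.** A clear exploratory label would also serve.

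The reply does not repair the undefined effect measure, the missing interaction tests for NSAID use and age, or the faulty rationale. The explorative label follows the 19-variable list and its reach over the three hypotheses is unclear, since those are said to be tested.

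**Conclusion.** The point holds in a limited form: wrong as written, and should be fixed. An odds ratio or relative risk cannot be computed for the primary endpoint or the other continuous scales without a cut-off that the documents do not give. A median cut would cost about 18 percentage points of power in a half-size stratum (62% to 44%, given SD 35, a 10-degree effect and the assumed split). Ratio measures could also suggest heterogeneity that does not exist in degrees. Models fitted separately in each arm are not evidence of effect modification. NSAID use and age lack an interaction test; drain use has one. The stated reason for waiving correction is invalid; the unadjusted familywise error over three hypotheses is about 14% if the tests are independent. The primary test is unaffected.

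**What to change.** In the addendum, before unblinding:

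1. For continuous endpoints, report the baseline-adjusted mean difference with 95% CI from the section 8 ANCOVA. Keep OR or RR for binary outcomes.
2. Extend the section 8 treatment-by-factor interaction to NSAID use and age, in one full-cohort model per factor. Drop the arm-by-arm models as evidence of effect modification.
3. Fix one age specification in advance that matches the hypothesis stated for patients over 60.
4. Delete the rationale for no correction. Either declare the three hypotheses exploratory or adjust across them, for example by Holm.
5. Do not read variables that arise after randomisation (transfusion, reinfusion, hospital stay) as effect modifiers. Transfusions and hospital stay are themselves secondary endpoints.

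The cost is wording and simple programming. The drawback is limited precision: a 10-degree interaction has only about 31–36% power at N = 500, and about 18–21% at the strictest Holm step (0.0167). Present the results as estimates with intervals, and do not read a non-significant interaction as showing that the effect is uniform.
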